### Other measures

Other measures to be collected at baseline, 6 and 12 months include:i)Hip Osteoarthritis Knowledge Scale [47], scored from 11 questions on a 5-point Likert scale with scores ranging from 11 to 55 where higher scores indicate greater knowledge about OA;ii)Attitudes toward self-management using the Patient Activation Measure (PAM-13) [48], scored from 13 statements rated on a 4-point Likert with higher scores indicating greater patient activation;iii)Brief Fear of Movement Scale for Osteoarthritis [49], scored from 6 statements on a 4-point Likert scale with scores ranging from 6 (minimal fear) to 24 (maximal fear);iv)Arthritis self-efficacy scale (pain subscale) [50], scored from 5 items on a 10-point NRS with the total presented as an average of the 5 items where higher scores indicate higher self-efficacy.

### Treatment adherence

A number of adherence measures will be collected from participants allocated to the *Better Hip* program. These include:i)Number of consultations with the physiotherapist, taken from consultation notes (0 to 6), reported as the mean (standard deviation) as well as the number and proportion of participants deemed to be adherent (≥4 consultations);ii)Duration of physiotherapist consultations (minutes);iii)Number of eligible participants (BMI > 27 kg/m^2^ and no exclusions for ketogenic VLED) choosing to undergo dietary intervention;iv)Number of consultations with the dietitian for those undergoing dietary intervention, taken from consultation notes (0 to 6), reported as the mean (standard deviation) as well as number and proportion of participants deemed to be adherent (≥4 consultations);v)Duration of dietitian consultations (minutes);vi)Adherence to the strengthening exercise program self-rated at 6 and 12 months on an 11-point NRS in response to the question: “Over the past 6 months, how much did you adhere to the strengthening exercise program provided to you by the physiotherapist?” with responses from 0=“not at all” to 10=“completely as instructed”;vii)Number of days strengthening exercises were performed in the previous fortnight self-reported at 6 and 12 months;viii)Perceived intensity of the strengthening exercise program self-rated at 6 months using the modified Borg Rating of Perceived Exertion CR-10 scale [33]. Participants will be asked “When performing your strengthening exercises over the past six months, how hard do you feel you have been working on average?” Scores range from 0 to 10 with higher scores indicating higher perceived intensity of exercise;ix)Adherence to a physical activity plan self-rated at 6 and 12 months on an 11-point NRS in response to the question: “Over the past 6 months, how much did you adhere to the physical activity plan provided to you by the physiotherapist?” with responses from 0=“not at all” to 10=“completely as instructed”.x)Adherence to a weight management plan (for those undergoing dietary intervention) self-rated at 6 and 12 months on an 11-point NRS in response to the question: “Over the past 6 months, how much did you adhere to the weight management plan?” with responses from 0=“not at all” to 10=“completely as instructed”.

### Other process measures

A number of other self-reported process measures will be collected at 6 months from the *Better Hip* group only (unless otherwise stated) including: Number of times website accessed (control group only); usefulness of physiotherapist consultations, dietitian consultations, OA educational resources, ‘My Exercise Messages’ app, activity tracker, weight loss program, weight loss/management resources, strengthening exercise program, physical activity plan, exercise/physical activity resources, each scored separately on an 11 point NRS with 0=“not at all useful” to 10 = “extremely useful”; use of ‘My Exercise Messages’ app in response to question “Did you use the ‘My Exercise Messages’ app to help you stick to your strengthening exercise program?” (Yes/No); satisfaction with the *Better Hip* program scored on a 5-point Likert scale with response options from “extremely unsatisfied” to “extremely satisfied” (those scoring “moderately” or “extremely” classified as “satisfied”) and; likelihood of recommending the *Better Hip* program to someone else with the same condition scored on a 5-point Likert scale with response options from “extremely unlikely” to “extremely likely” (those scoring “moderately” or “extremely” classified as “likely”). The control group will also be asked to self-report at 6 and 12 months whether they have undertaken any regular exercise for their hip (defined as 2 or more times per week for at least 1 month) and the type of such exercise.

### Descriptive measures

Baseline self-reported descriptive measures include age, height, BMI, gender, country of birth, ethnicity, geographical location, education level, current employment status, occupation, weekly earnings before tax, symptom duration, time since first visit to doctor for hip pain, comorbidities assessed using the Self-Administered Comorbidity Questionnaire [51], history of hip surgery, and treatment expectation assessed on a 5-point ordinal scale.

### Treatment fidelity

Consultations with physiotherapists and dietitians in the *Better Hip* group will be audio-recorded and files will be stored on a secure password-protected cloud-based system. Bespoke semi-structured consultations notes will be completed online on REDCap™ by physiotherapists and dietitians for each consultation. Notes will be scrutinised by research staff for clinician adherence to protocols.

Fidelity, as determined from the clinician consultation notes, will be reported as the number and proportion of participants where the physiotherapist: i) prescribed a strengthening exercise program; and ii) prescribed a physical activity plan, and where the dietitian: i) discussed the use of meal replacements; ii) discussed ketogenic principles for preparing the third meal during the ketogenic VLED phase; iii) discussed transition to healthy eating; and vi) discussed healthy eating principles. The number and proportion of participants where the clinicians delivered the core behaviour change techniques will be reported for: goal setting; problem solving; review behaviour goals; feedback on behaviour; feedback on outcomes of behaviour; instruction on how to perform the behaviour; and information about health consequences.

### Adverse events

Related adverse events are defined as “any problem experienced in the study hip or elsewhere in the body deemed to be a result of participating in the trial and at least one of i) caused negative/adverse symptoms/effects for two days or more, and/or ii) resulted in the participant seeking treatment from a health professional”. Adverse events will be ascertained by survey questions to participants at 6 and 12 months.

A serious adverse event is defined as any untoward medical occurrence that; i) results in death; ii) is life-threatening; iii) requires hospitalisation or prolongation of existing inpatient hospitalisation; iv) results in persistent or significant disability or incapacity; v) is a congenital anomaly or birth defect, or; vi) any other important medical condition which, although not included in the above, may require medical or surgical intervention to prevent one of the outcomes listed. Due to the low-risk nature of the interventions in this trial, related serious adverse events are extremely unlikely. Participants, dietitians and physiotherapists will be advised to report any serious adverse events to the Trial Coordinator as soon as they can by telephone or email, which will be documented and reported to the Sponsor (University of Melbourne) within 24 hours of the research staff becoming aware of the event.

Any adverse events reported by telephone/email or in questionnaires will be reported to the Internal Trial Monitoring Committee, including the Chief Investigator who will be responsible for deciding what action, if any, is needed on a case-by-case basis. All recorded adverse events will also be reported as blinded data to the Data Safety and Monitoring Committee for the study. The Internal Trial Monitoring Committee and the Data Safety and Monitoring Committee will collectively determine whether reported adverse events are likely to be related to the intervention.

We will report the number and proportion of participants who: withdraw from the study due to a related adverse event; experience one or more serious related adverse events and their types; and experience one or more non-serious related adverse events and their types.

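### Serious adverse events are collected whatever their cause, but the reporting list covers only events judged related, a judgement that depends on the arm

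*Protocol article*

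**What the plan says.** All of the following is in the Adverse events section of the protocol article unless another section is named.

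- **Serious events, definition.** The definition begins "A serious adverse event is defined as any untoward medical occurrence that" and goes on to list outcomes such as death and hospitalisation. Relatedness is no part of it.
- **Serious events, collection.** "Participants, dietitians and physiotherapists will be advised to report any serious adverse events to the Trial Coordinator as soon as they can". The request covers any serious event, not only related ones.
- **Other adverse events.** The only definition given is for related events: "any problem experienced in the study hip or elsewhere in the body deemed to be a result of participating in the trial", with a further condition on duration or on seeking treatment. On collection: "Adverse events will be ascertained by survey questions to participants at 6 and 12 months". This is not restricted to one arm.
- **Judgement.** Reported events go to the Internal Trial Monitoring Committee, which includes the chief investigator. "All recorded adverse events will also be reported as blinded data to the Data Safety and Monitoring Committee for the study". The two committees "will collectively determine whether reported adverse events are likely to be related to the intervention".
- **Reporting.** The list has three items: withdrawals due to a related event, and participants who "experience one or more serious related adverse events and their types; and experience one or more non-serious related adverse events and their types".

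Elsewhere, the section on randomisation and blinding says that participants are not blinded. The section on the control describes a website whose content includes exercise and weight loss.

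**The concern.** Data gathered without regard to cause pass through a causal judgement before they reach the published safety results. Randomisation makes the arms comparable for all-cause events. It does not do so for events filtered by a judgement whose outcome depends on what each arm received. A muscle strain, a fall or a gastrointestinal complaint is more readily put down to a strengthening and diet programme than to a website.

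The reported counts could then err in either direction. Background events attributed to Better Hip would look like harm. A real excess of serious events, each judged unrelated one at a time, would be missing from the safety list. The Discussion says that the trial's measures will give insight into safety, and the Dissemination section expects the insurer to scale up the programme if it is effective, so the safety table will be used.

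**Working it through.** The plan states no safety figure, so there is none to reproduce. The check sets the rules side by side and then illustrates what the filter does.

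**1. Scope at each stage**

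| Stage | Serious events | Other events |
|---|---|---|
| Definition | any cause | related only |
| Collection | any cause | 6- and 12-month surveys (wording not shown) |
| Sent to the monitoring committee | all recorded | all recorded |
| Reporting list | related only | related only |

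For serious events the scope narrows between collection and reporting.

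**2. Two tests of relatedness.** The definition asks whether an event results from taking part in the trial. The committees judge relation to the intervention. An event in a control participant meets the second test less easily than the first.

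**3. Effect of the filter.** Let *p* be the true all-cause risk of an event in an arm and *q* the probability that such an event is judged related. The expected reported count is 106 × *p* × *q*, with 106 per group from the Trial sample size section. The expected reported difference is *p*₁*q*₁ − *p*₀*q*₀, with 1 for Better Hip and 0 for control. The document gives neither *p* nor *q*; all values below are assumptions.

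Equal true risk in both arms, so the correct difference is 0:

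| *p* (both arms) | *q*₁, *q*₀ | Reported, Better Hip v control | Difference |
|---|---|---|---|
| 5% | 30%, 5% | 106 × 0.05 × 0.30 = 1.6 v 106 × 0.05 × 0.05 = 0.3 | 0.05 × 0.25 = 1.25 points |
| 20% | 50%, 5% | 106 × 0.20 × 0.50 = 10.6 v 106 × 0.20 × 0.05 = 1.1 | 0.20 × 0.45 = 9.0 points |
| 30% | 50%, 5% | 106 × 0.30 × 0.50 = 15.9 v 106 × 0.30 × 0.05 = 1.6 | 0.30 × 0.45 = 13.5 points |
| 20% | 50%, 50% | 10.6 v 10.6 | 0 |

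The spurious difference comes entirely from unequal *q*.

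A real excess, with *p*₁ = 20% and *p*₀ = 10%: all-cause counts are 106 × 0.20 = 21.2 against 106 × 0.10 = 10.6, a difference of 10 points. If 5% of events are judged related in both arms, the reported counts are 21.2 × 0.05 = 1.1 against 10.6 × 0.05 = 0.5, a difference of 0.5 points. Even an evenly applied filter can hide the excess.

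**4. Reporting routes for serious events.** Participants in both arms can report. Trial physiotherapists and dietitians are a further route in Better Hip only: six physiotherapy consultations for everyone, plus six dietitian consultations for those who are eligible and choose the diet, so 6 to 12 against none in control. The document gives nothing from which the effect on counts could be estimated.

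**The case against.** - **Related control events.** A reader might infer that they are impossible by definition. They are not: the definition refers to taking part in the trial, and the website covers exercise and weight loss. They are less likely, not excluded.
- **The masked committee.** A reader might infer that a committee given blinded data cannot judge relatedness. The document does not say what detail it sees. Event type and timing allow some judgement, and masking limits attribution driven by the arm. What stands is that no masking is stated for the other committee, which shares the decision.
- **Clinician reports.** A reader might infer that these inflate Better Hip counts. Clinicians are asked to report serious events only, participants are asked as well, and the surveys have no restriction by arm. An extra route exists, but its effect is unknown.
- **Other routes for harm.** Serious events go to the sponsor within 24 hours. The monitoring committee receives all recorded adverse events and a study report every 3 months. Study-hip replacement and oral pain medication are compared by arm, and hospital use is collected for the economic evaluation. So a real excess need not go unnoticed. But oversight is not publication, the economic results are reported separately, and the secondary outcomes are not a count of serious events.
- **Fuller tables elsewhere.** The list does not say that nothing else will be reported, no between-arm safety test is planned, and the article commits to CONSORT and to a published analysis plan. This is the strongest objection. It does not remove the point, because the article does not leave safety reporting open: it gives an explicit list in which every item is limited to related events.

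**Conclusion.** The point holds for the reporting list. Serious events are collected regardless of cause, and what the article commits to publish is filtered by a judgement that depends on the arm. The resulting bias cannot be signed from the document. Its size depends on event rates and attribution probabilities that the document does not give. Under the assumed values above, the spurious difference runs from 1.25 to 13.5 points when true risks are equal, and a true 10-point excess can shrink to 0.5 points.

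The documents do not support the stronger conclusions that the trial allows no safety comparison at all, or that the control count is zero by construction. The data for a fair all-cause comparison of serious events are largely being collected; they are simply not on the list. The primary efficacy results are unaffected. This should be changed before reporting, but it does not threaten the trial's main conclusion.

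**What to change.** Keep the three related-event items and add, for each arm with its denominator:

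- the number and proportion of participants with any serious adverse event regardless of relatedness, with types;
- the same for all recorded adverse events, as collected;
- relatedness as an additional column, not as a condition for entry to the table;
- the source of each report (participant or survey, as against clinician), so that the arms can be compared on the participant-reported sources common to both.

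No change to the survey question is required. Its wording is not shown, and a change after recruitment began in June 2022 could make ascertainment uneven over time. If the question asks about related events only, the table of non-serious events should say so.

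The cost is reporting wording and a few more table columns, with no new data. The downside is that more background events are tabulated.

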### Health economic measures and evaluation

We will conduct economic evaluations (led by AH) with results reported separately to the main trial outcomes. These will use data from Medicare/Pharmaceutical Benefits Scheme and Medibank and will assess and compare cost-effectiveness of *Better Hip* including: i) cost per extra person with a clinically significant improvement in pain and function; and ii) per quality-adjusted life years (QALY) gained for *Better Hip* group compared to control at 12 months.

Health care expenditure for each participant will be extracted from Medicare Benefit Schedule (MBS), Pharmaceutical Benefit Scheme (PBS) and Medibank data for 12 months prior to baseline and for 24 months after enrolment. The MBS collects information on medical visits and procedures, and the associated costs. The PBS collects information on prescription medicines filled at pharmacies, and Medibank collects information on member hospital, medical and ancillary services for claims made against their Medibank membership. We will seek participants’ consent to access their Medibank data and their MBS and PBS data from the Australian Government Department of Human Services. Public hospital admission/attendance will be self-reported at baseline, 6 and 12 months via a bespoke questionnaire asking number, reason for and length of public hospital admissions in the last 6 months. Participants will also be asked if they attended an emergency department and/or any outpatient appointments at a public hospital.

For those in employment, work productivity will be assessed using the World Health Organisation Health and Work Performance Questionnaire (clinical trials version) [52].

QALYs will be calculated based on utility scores using the AQoL-8D at baseline and 12 months. Difference in health care usage and productivity lost between baseline and 12 months will be compared, as will the association between utility gains (AQoL-8D) and productivity.

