### Outcome measures

Participant-reported outcomes will be collected online via REDCap data capture platform at baseline, 6 months and 12 months. All participants who complete the 12-month re-assessment will be given a $50 gift voucher as compensation for the considerable time they have invested in the trial. An online survey for follow-up of primary and secondary outcomes will also be conducted at 2 years post randomisation. These longer-term results will be reported separately to the main trial results and will occur after analysis of the main trial data.

Primary outcomes are reliable and valid measures recommended for use in clinical trials of hip OA [41]. These will be measured at baseline, 6 and 12 months, and include i) change in average severity of hip pain on walking in the past week measured on an 11-point NRS, where 0 = “no pain” and 10 = “worst pain possible”; ii) change in physical function subscale of the Western Ontario and McMaster Universities Osteoarthritis Index (WOMAC) [42] with scores from 0 to 68, where higher scores indicate greater dysfunction. Conclusions about effectiveness will be based on the 6 month time point change in the primary outcomes.

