The secondary outcomes will be measured at baseline, 6 and 12 months unless otherwise indicated and include:i)Change in Hip dysfunction and Osteoarthritis Outcome Score (HOOS) [43] subscale of pain with normalised scores ranging from 0 to 100, with 100 indicating no symptoms;ii)Change in HOOS [43] subscale of hip-related quality of life, with normalised scores ranging from 0 to 100, with 100 indicating better quality of life;iii)Change in HOOS [43] subscale of function, sports and recreational activities with normalised scores ranging from 0 to 100, with 100 indicating better function;iv)Change in self-reported body weight measured in kilograms;v)Change in health-related quality of life using the Assessment of Quality of Life instrument (AQoL-8D) [44], a 35-item instrument with scores ranging from − 0.04 to 1.0, with higher scores indicating better quality of life;vi)Change in physical activity levels evaluated using the Physical Activity Scale for the Elderly (PASE) [45] with scores from 0 to 400, where higher scores indicate greater levels of physical activity;vii)Perceived global rating of overall change in hip condition scored on a 7-point Likert scale from ‘much worse’ to ‘much better’ [46] at 6 and 12 months. Participants who indicate that they are “moderately better” or “much better” will be categorised as ‘improved’;viii)Self-reported hip replacement procedures, where participants will be asked if they have had a hip joint replacement since their study enrolment on the study hip at 6 and 12 months;ix)Willingness to undergo hip replacement surgery self-rated using a 5-point Likert scale with anchors “definitely not willing” and “definitely willing”. Participants indicating ‘probably willing’ or ‘definitely willing’ will be classified as ‘willing’;x)Use of oral pain medications self-reported and defined as one or more of analgesics (paracetamol combinations) and/or oral non-steroidal anti-inflammatory drugs and/or oral glucocorticoids and/or oral opioids taken at least once a week in the prior month for hip pain.

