## Discussion

This protocol describes the background, aims and methods for a two-group, parallel design RCT aiming to evaluate the effectiveness of a 6-month telehealth-delivered, clinician-supported lifestyle management program (*Better Hip*) on the primary outcomes of change in hip pain while walking and physical function at 6 months, compared with an information-only control for people with hip OA. The effects of the program on these primary outcomes at 12 months as well as on other clinical outcomes at 6 and 12 months will also be evaluated. A range of other measures will provide insights into the safety, feasibility, acceptability of and engagement with this innovative remotely-delivered model of service delivery that focuses on core recommended hip OA treatments of education, exercise/physical activity, and for those with overweight and obesity, weight loss. A separate health economic evaluation at 12-months will inform implementation decisions while a separate survey to the main trial will follow-up participants at 2-years to determine longer-term outcomes. Such a service model has the potential to increase patient access to evidence-based lifestyle management programs.

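### The QALY calculation names only baseline and 12-month AQoL-8D utilities, although the 6-month value is collected; unless the utility difference at 12 months is twice that at 6 months, the QALY gain and the cost per QALY change

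*Protocol article*

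**What the plan says.** In the protocol article, Health economic measures and evaluation, one of the two cost-effectiveness results is the cost "per quality-adjusted life years (QALY) gained for" the *Better Hip* group against control at 12 months. For its denominator the section states: "QALYs will be calculated based on utility scores using the AQoL-8D at baseline and 12 months".

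The Outcome measures section gives a fuller collection schedule:

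- "Participant-reported outcomes will be collected online via REDCap data capture platform at baseline, 6 months and 12 months".
- "The secondary outcomes will be measured at baseline, 6 and 12 months unless otherwise indicated". Item v of that list is "Change in health-related quality of life using the Assessment of Quality of Life instrument (AQoL-8D"), and no different schedule is given for it.

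The 6-month utility is therefore available. Nothing in the article brings it into the QALY or explains leaving it out. In the same economic section, another input is listed at all three times: "Public hospital admission/attendance will be self-reported at baseline, 6 and 12 months via a bespoke questionnaire".

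The Discussion describes a "6-month telehealth-delivered, clinician-supported lifestyle management program", so the 6-month assessment falls at the end of the program. It is also the main time point of the trial: "Conclusions about effectiveness will be based on the 6 month time point change in the primary outcomes".

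**The concern.** A QALY over 12 months is the area under the utility curve for that year. With utilities at baseline and 12 months only, the natural calculation is a straight line between them, and whatever was measured at 6 months has no influence. With three points, the middle one carries the most weight because it bounds both halves of the year.

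The omitted measurement is the one taken as the program ends. The suggested timetable has the last physiotherapy consultation in week 21 and the last dietitian consultation in weeks 19 to 23. Contact with clinicians, and its cost, therefore falls in the first half of the year. A cost-per-QALY ratio that counts those costs in full but ignores the utility measured at the end of that half can be materially wrong. The Discussion says the economic evaluation will inform implementation decisions, and the Dissemination section says the insurer is likely to scale the program up if it is effective.

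**Working it through.** The protocol states no utility difference, QALY gain or cost per QALY, so there is no figure of its own to reproduce. The check compares the two calculation rules.

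**Inputs from the protocol article:** utilities named for the QALY, baseline and 12 months; AQoL-8D collected at baseline, 6 and 12 months; horizon, 12 months (1 year).

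**Assumptions:** linear interpolation between measurements (the article gives no formula); no between-arm difference at baseline; d6 and d12 are the between-arm differences in utility at 6 and 12 months. The values of d6 and d12 below are illustrative only.

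**Two points.** Gain = 0.5 × (0 + d12) × 1 year = 0.5·d12.

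**Three points.** Gain = 0.5 × (0 + d6) × 0.5 year + 0.5 × (d6 + d12) × 0.5 year = 0.25·d6 + 0.25·d6 + 0.25·d12 = 0.5·d6 + 0.25·d12.

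**Error of the two-point rule.** 0.5·d12 − (0.5·d6 + 0.25·d12) = 0.25·d12 − 0.5·d6. This is zero only when d12 = 2·d6, that is, when the difference grows in a straight line from baseline to 12 months. It is negative (gain understated) when d12 < 2·d6 and positive (gain overstated) when d12 > 2·d6.

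**Effect on cost per QALY.** For a fixed incremental cost and d12 above zero, the two-point ratio divided by the three-point ratio is (0.5·d6 + 0.25·d12) / (0.5·d12) = d6/d12 + 0.5. Only the shape of the trajectory matters, not the absolute utility values.

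| d6 | d12 | Two points | Three points | Two ÷ three | Cost per QALY multiplied by |
|---|---|---|---|---|---|
| 0.04 | 0.04 (held) | 0.020 | 0.030 | 0.67 | 1.5 |
| 0.04 | 0.03 | 0.015 | 0.0275 | 0.55 | 1.83 |
| 0.04 | 0.02 (half lost) | 0.010 | 0.025 | 0.40 | 2.5 |
| 0.04 | 0.01 | 0.005 | 0.0225 | 0.22 | 4.5 |
| 0.04 | 0 (all lost) | 0 | 0.020 | 0 | undefined |
| 0.04 | 0.05 (some growth) | 0.025 | 0.0325 | 0.77 | 1.3 |
| 0.02 | 0.04 (linear growth) | 0.020 | 0.020 | 1.00 | 1.0 |
| 0.02 | 0.05 (more than doubles) | 0.025 | 0.0225 | 1.11 | 0.9 |
| 0 | 0.04 (late effect only) | 0.020 | 0.010 | 2.00 | 0.5 |

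In the row with some growth after 6 months, the two-point rule still understates the gain. The direction reverses only once the 12-month difference is more than twice the 6-month difference.

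**The case against.** **The wording may be loose.** The sentence does not say that the 6-month value is excluded. The sentence that follows it uses baseline and 12 months to mark a comparison window for health care use and productivity, and a fuller economic plan may exist. So it is possible that the authors meant a 12-month horizon. This reading is strained: the sentence names the times at which utilities are taken, and the same section writes out all three times for public hospital use. If three points were intended, the sentence still needs correcting.

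**The formula is supplied here.** The article states no area-under-the-curve or interpolation rule. That stands, and it is why linear interpolation is listed as an assumption. It is the usual choice with two points, but the ratios depend on it.

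**The direction is not established.** A reader might infer that the benefit peaks at 6 months and that the planned cost per QALY is bound to be too high. The documents do not support that. They make 6 months the primary time point and describe a 6-month program, but they predict no utility trajectory. The program also aims at lasting behaviour change and has a weight-maintenance phase. A reader might equally infer that any further growth after 6 months reverses the error; the algebra shows that it does not until the difference more than doubles.

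**The reach is limited.** The evaluation is reported separately, the other cost-effectiveness measure (cost per additional person with a clinically significant improvement) does not use QALYs, and the 6-month data will exist whatever the sentence says. All of this stands and bears on severity.

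**Conclusion.** The point holds. The article fixes the QALY on two of the three utility measurements it collects and gives no reason for leaving out the one at the end of the program.

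Under linear interpolation and equal baselines, the two-point gain is right only if d12 = 2·d6. It is too low below that and too high above it. If the effect is reached by 6 months and fully held, the gain is one third too low and the cost per QALY 1.5 times too high; if half is lost by 12 months, the cost per QALY is 2.5 times too high. These are illustrations, since the documents give no utility differences.

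It should be fixed, but it is not a fault that threatens the trial. The primary outcomes, the sample size, the type I error and the 6-month conclusion on effectiveness are untouched. Nothing is lost irrecoverably, because the rule can be corrected at any time before the economic analysis.

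**What to change.** Replace the sentence with: *QALYs over 12 months will be calculated for each participant as the area under the curve (trapezoidal rule) through AQoL-8D utilities at baseline, 6 months and 12 months.*

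The cost is one sentence, made before the economic analysis begins. No data collection changes.

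The authors may also state that the between-group QALY difference will be adjusted for baseline utility. That is an optional addition, which an article may reasonably leave to a fuller plan, and it does not correct an error here.
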